## Abstract

**Background:**

Non-specific chronic low back pain (NSCLBP) is a major public health and global socioeconomic burden associated with a complex interplay of biopsychosocial factors. Despite scientific signs of progress, treatment of NSCLBP often tends to stick to a biomechanical model, without targeting psychological and social factors. To enhance the clinical efficacy of usual physiotherapy for NSCLBP, the development of clinical strategies is to be pursued. This study aims to assess the effectiveness of multidimensional physiotherapy based on a biopsychosocial approach compared to usual care physiotherapy, on clinical findings and electroencephalography spectrum in non-specific chronic low back pain.

**Methods:**

This study is a triple-blind, two-arm (1:1) randomized controlled trial with a 4 months follow-up. Seventy NSCLBP patients will be randomly allocated to either the experimental (multidimensional physiotherapy) or the active control group (usual physiotherapy); each group will receive 6 weeks of physiotherapy. The main outcome is pain and secondary outcomes are brain function, quality of life, disability, lumbar flexion range of motion, and psychosocial correlates. Assessment will be performed at baseline, post-treatment, and at 1 and 4 months follow-up.

**Discussion:**

Findings may provide evidence on the effectiveness of multidimensional physiotherapy on clinical findings and brain characteristics and might provide evidence towards showing the role of brain and biopsychosocial factors on chronic pain.

**Trial registration:**

ClinicalTrials.gov NCT04270422, Registered on 17 February 2020, IRCT Identifier: IRCT20140810018754N11

## Introduction

### Background and rationale {6a}

Low back pain (LBP) is the most frequent self-reported, costly, and debilitating type of musculoskeletal pain that imposes significant health and economic problems [1, 2]. The prevalence of LBP estimates 33% for point prevalence, 65% for 1 year prevalence, and 84% for lifetime prevalence [3, 4]. Eighty to 90% of LBP is self-limiting, while almost 20% of the cases become persistent and disabling and negatively affect many aspects of daily life [3, 5, 6]. Evidence shows that only 8–15% of patients with LBP have an identified pathoanatomical diagnosis (specific LBP), resulting in the majority being diagnosed as having non-specific LBP [7]. Among this non-specific population, a small but considerable group becomes chronic and disabled, which is labeled non-specific chronic low back pain (NSCLBP) [1, 8]. The effective management of NSCLBP is a major concern for people, the economy, and society as a whole [1, 7, 9]. NSCLBP is no longer considered a purely structural, anatomical, or biomechanical disorder of the lumbar spine. Instead, there is strong evidence that NSCLBP is associated with a complex interaction of factors involve structural or biomechanical, cognitive (e.g., unhelpful beliefs, catastrophizing, maladaptive coping strategies, low self-efficacy), psychological (e.g., fear, anxiety, depression), lifestyle (e.g., immobility, sleep problems), and social (e.g., work and family issues) factors [1, 8, 10–13]. Consequently, NSCLBP treatment guidelines generally acknowledge a shift from biomedical models to the biopsychosocial model. In this approach, the cognitive, psychological, and social dimensions of pain are adopted in addition to the physical and pathoanatomical dimensions [1, 6, 14].

The perception of pain is the result of a complex, dynamic system. The relationship between nociceptive information and pain is profoundly impressed by affective and cognitive factors. A specific region of the cortex that is responsible for pain processing has not yet been found; however, a complex network of brain regions known as a pain matrix has been identified. According to the neuromatrix theory of pain, chronic pain is considered a multidimensional experience and needs new forms of multidimensional treatment. The area of the brain involved in pain experience is a large and widespread network of neurons that consists of loops between the thalamus and cortex, as well as between the cortex and limbic system. These loops are not just for pain perception but also are involved in other sensory, motor, and cognitive functions [15, 16]. Functional MRI studies have shown that spontaneous back pain in CLBP patients does not activate the areas of the pain matrix typically seen during noxious stimulation, which supports the notion that chronic pain may not be caused by the nociceptive process [17].

Although growing knowledge exists on the peripheral and spinal neuronal mechanism of pain chronification processes, little is known about the accompanying neural mechanisms of chronic pain [18]. Recent studies have identified a relationship between chronic neurogenic pain and the presence of specific electroencephalography (EEG) pattern called thalamocortical dysrhythmia (TCD). TCD is characterized by a common oscillatory pattern in which resting-state alpha activity is replaced by cross-frequency coupling of low- and high-frequency oscillations. Despite many advances in the treatment of chronic pain, major challenges remain, and the main cause is the lack of precise diagnosis of the underlying cause of chronic pain. The somatosensory cortex and thalamocortical loop appear to be the best candidate for understanding chronic pain because these regions are most active in processing sensory information and have a strong role in processing pain [18–20].

Various non-surgical treatments have been suggested for NSCLBP. These include non-steroidal anti-inflammatory drugs, patient education, hydrotherapy, manual therapy, physiotherapy, acupuncture, and cognitive-behavioral therapy [1, 9]. Physiotherapy is one of the common interventions for the management of LBP [21–26]. General exercises and patient education have the most evidence and use as usual physiotherapy [9, 27–29]. Although routine physiotherapy helps patients recover, about one third of patients run a recurrence of LBP within a year. We hypothesize that usual LBP physiotherapy relies solely on the biomechanical dimension of health and ignores the psychosocial aspects [3, 22, 30, 31].

In the present study, the effect of a multidimensional treatment based on the biopsychosocial approach will be compared with a usual care physiotherapy treatment on pain and function, brain function, and pain psychosocial correlates in chronic nonspecific low back pain.

### Objectives {7}

The overall objective of this study is to demonstrate the impact of multidimensional treatment in the management of CNSLBP. The specific objectives are:
Primary objective: Effect of a multidimensional treatment on pain compared to usual care physiotherapySecondary objectives:Effect of a multidimensional treatment on brain function compared to usual care physiotherapyEffect of a multidimensional treatment on lumbar flexion ROM compared to usual care physiotherapyEffect of a multidimensional treatment on quality of life compared to usual care physiotherapyEffect of a multidimensional treatment on psychological correlates of pain compared to usual care physiotherapy

### Trial design {8}

The present study is a 4-month, triple-blind, randomized, controlled, parallel trial that will be carried out between December 2020 and November 2022. Patients with NSCLBP will be enrolled in a 6-week physiotherapy program organized in IRAN (Iran University of Medical Science). More specifically multidimensional physiotherapy will be compared to usual physiotherapy. The outcome will be assessed at baseline, after 6 weeks of treatment, and at 1 and 4 months follow-up. The participant flowchart through the study is shown in Fig. 1.

**Fig. 1 Fig1:**
[figure not shown]
Flow chart of research design (CNSLBP, chronic non-specific low back pain; NRS, Numerical Rating Scale; PCS, Pain Catastrophizing Scale; SF-36, Medical outcomes 36 Health Service Survey; TSK, Tampa Scale for Kinesiophobia; ODI, Oswestry Disability Index; FABQ, Fear Avoidance Beliefs Questionnaire; ROM, range of motion)

## Methods: participants, interventions, and outcomes

### Study setting {9}

The study population will include approximately 70 CNSLBP patients. Participants will be recruited by the participating research groups from the Iran University of Medical Science’s hospitals and via adverts. This study will be conducted in the physiotherapy clinic in the School of Rehabilitation Sciences at the Iran University of Medical Sciences, Tehran, Iran.

### Eligibility criteria {10}

Patients will be eligible for this study if they have the following: age between 18 and 50, permanent or intermittent local pain between L1 to gluteal fold without any radicular pain for 3 months or more and between 3 and 7/10 based on the Numeric Rating Scale (NRS), disability based on the Oswestry Disability Index (ODI) between 20 and 60, fear of movement based on the Tampa scale for Kinesiophobia > 37, elementary level of education, and Native Persian speaking. The most important exclusion criteria are as follows: any evidence of specific medical diagnosis include spondylolisthesis, fracture, tumor, or inflammation disease; rheumatoid disease, fibromyalgia, neuropathy, and progressive neurological disease; history of headache, dizziness, nausea, epilepsy, migraines, and mental disorders; history of lumbar surgery in the past 3 years; the Beck Anxiety Inventory > 26; the Beck Depression Inventory II > 29; pregnancy; and having other therapies during the present research. The drop-out criteria are as follows: the presence of any condition that interferes with the intervention or assessment, participate in any other treatment during the interventions, inclusion or exclusion criteria are violated, and a patient requests to be removed from the trial.

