### Sample size {14}

Sample size calculations were performed with G*Power 3.1.9.4 (Düsseldorf, Germany) based on the therapy effects on pain and accounting for a 10% loss to follow-up after 4 months. Calculations were based on one-tailed testing with alpha set in 0.025, partial η2 = 0.04, and the desired power of 0.95. The allocation ratio (N2/N1) was defined as 1, resulting in 35 patients in the intervention group and 35 in the control group.

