## Statistical methods

### Statistical methods for primary and secondary outcomes {20a}

Data analysis will be performed using SPSS (version 22) and STATA (version 14.2). Baseline characteristics will be summarized with standard descriptive statistics. Categorical variables will be described with percent and counts. Continuous variables will be described with means and standard deviations. Statistical analysis of the primary and secondary outcomes will be based on the intention-to-treat principle including all randomized patients using an analysis of variance/covariance (ANOVA/ANCOVA). A model including baseline as continuous covariate and group as fixed factors will be used with using Bonferroni post hoc analyses and adjusting for differences in patients’ characteristics at baseline where appropriate will be done. Subgroup analysis of pain catastrophizing variable will be done. For all statistical tests, the significance level will be set at 0.05. Mean difference and standardize Mean difference and their 95% confidence intervals (Cohen’s *D*) will be calculated as are effect sizes.

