### Methods in analysis to handle protocol non-adherence and any statistical methods to handle missing data {20c}

Not applicable

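### Post-randomisation drop-out criteria and an expected 10% loss stand beside an intention-to-treat promise and no missing-data method, so the analysis can become complete-case

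*Protocol article*

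**What the plan says.** **Who leaves.** Eligibility criteria {10}: "The drop-out criteria are as follows: the presence of any condition that interferes with the intervention or assessment". The list continues: "participate in any other treatment during the interventions, inclusion or exclusion criteria are violated, and a patient requests to be removed from the trial". The exclusion criteria in the same section include "having other therapies during the present research", an event that can only occur once the patient is in the study. Section {11d} prohibits relevant concomitant care during the trial.

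**How many.** Sample size {14}: the calculation was done "accounting for a 10% loss to follow-up after 4 months" and gives 35 patients per group.

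**Who is analysed, and how.** Statistical methods {20a}: the analysis "will be based on the intention-to-treat principle including all randomized patients using an analysis of variance/covariance (ANOVA/ANCOVA"). It continues: "A model including baseline as continuous covariate and group as fixed factors will be used".

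**What happens to gaps.** Section {20c}, on non-adherence and missing data, reads *Not applicable*. So do {11b}, on discontinuing allocated treatment, and {18b}, on retention and complete follow-up. Nowhere does the article say whether a patient who meets a drop-out criterion is still assessed, or how that patient enters the analysis.

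**The concern.** Missing data and non-adherence cannot be inapplicable in a protocol that creates drop-outs by rule and budgets for them. Including everyone randomised needs either an outcome for everyone or a stated method for those without one. The article provides neither.

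The primary outcome is pain. A patient whose pain persists has a reason to seek other care, and doing so meets a drop-out criterion. During the interventions this is explicit. During follow-up it comes about through the exclusion criterion on other therapies together with the rule on violated criteria. If such patients leave and are no longer measured, the completers are no longer the randomised groups. The arm that loses more of its poor responders then looks better than it is. An analysis plan written later cannot recover pain scores that were never collected, so the matter belongs in the protocol.

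**Working it through.** **1. The statements side by side**

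| Section | Statement | Consequence |
|---|---|---|
| {10} | Drop-out for other treatment, violated criteria, an interfering condition, or patient request | Randomised patients can leave after allocation |
| {11b} | Discontinuation criteria not applicable | Unclear whether {10} ends treatment, follow-up or both |
| {14} | 10% loss | 0.10 × 70 = 7 patients without a 4-month score |
| {20a} | All randomised patients; baseline and group in the model | Needs an outcome for all 70 |
| {20c} | Not applicable | No method for the 7 |

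A model of outcome on baseline and group has no contribution from a patient whose outcome is missing. Without a further method, the patients analysed are those observed.

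**2. The protocol's own figure**

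Inputs from {14}: partial η² = 0.04, alpha 0.025, power 0.95, 1:1 allocation. From the outcomes section: four assessments. Assumed, because not stated: correlation 0.5 between assessments, sphericity 1, and a repeated-measures within-between interaction test.

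- f² = 0.04 / 0.96 = 0.0417
- λ = f² × N × 4 / (1 − 0.5). With N = 62, λ = 20.67
- F test on (2 − 1)(4 − 1) = 3 and (62 − 2)(4 − 1) = 180 degrees of freedom: power 0.956
- N = 62 is the smallest even number reaching 0.95 (N = 60 gives 0.948)
- 62 / 0.90 = 68.9, so 69, rounded up to 70 for equal arms

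The stated 70 is reproduced. With all 70 analysed, power is 0.976; with 62 completers it is 0.956. The planned loss is therefore covered for power. What remains is bias and the analysis set.

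**3. How large the bias could be**

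The protocol has no figure for this, so the following is an illustration. Assumptions: no true effect; normal outcomes; the odds of dropping out rise by a factor of 1.5 to 3 per SD of worse pain, equally in both arms; analysis of completers only. Bias is the difference between arms in the completers' mean.

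| Loss in the two arms | Difference | Bias (SD) |
|---|---|---|
| 10% and 10% | 0 points | 0 |
| 15% and 5%, or 20% and 10% | 10 points | 0.04 to 0.09 |
| 20% and 0%, or 30% and 10% | 20 points | 0.08 to 0.19 |
| Same, only the worst outcomes leave | 10 points | 0.15 to 0.17 |
| Same, only the worst outcomes leave | 20 points | 0.30 to 0.35 |

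At an assumed SD of 1.5 to 2.0 on the 0–10 pain scale:

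- a 10-point difference gives 0.04 × 1.5 = 0.06 to 0.09 × 2.0 = 0.18 points
- a 20-point difference gives 0.08 × 1.5 = 0.12 to 0.19 × 2.0 = 0.38 points

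The bias favours whichever arm loses more.

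**The case against.** The best case for the protocol is that its only explicit statement about the analysis set is the one in {20a}, which includes everyone randomised. No section says that drop-outs leave the analysis or stop being assessed. *Not applicable* is also used loosely in this article: {18a}, on outcome assessment, carries the same answer although the outcomes section describes assessment in detail. Allowing for loss in the sample size is ordinary practice beside an intention-to-treat analysis. A missing-data method may stand in a document not shown.

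Much of this stands. Exclusion from the analysis is an inference, and the 10% allowance alone contradicts nothing. What does not go away is that the drop-out list is fixed in the protocol, that it names events after randomisation, and that the one place reserved for dealing with them declares them irrelevant.

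Four stronger readings are tempting and not supported:

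- *That the analysis will certainly be an outcome-dependent complete-case analysis.* It can become one. Dependence on outcome is plausible for patients seeking other care, less so for ineligibility discovered late.
- *That a patient whose pain moves outside 3 to 7 must be removed, because that range is an inclusion criterion.* Violated criteria normally means found to have been ineligible. Read as a continuing rule it would also remove treatment successes, and nothing suggests that was meant.
- *That each visit is analysed separately.* Section {20a} does not say so.
- *That the bias can be stated as a share of the planned effect.* Reading partial η² = 0.04 as a two-group difference (d = 0.41) needs 312 patients before drop-out, so it is not the effect behind the 70.

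**Conclusion.** The point holds as a conflict between stated rules. Followed as written, {10} and {20c} can lose primary-outcome data from randomised patients, and the model in {20a} has no means of including them. Whether this biases the comparison depends on who leaves and from which arm. It is about zero if loss is equal and similar in both arms. Under the assumptions shown it is up to about 0.2 SD with a 20-point difference in loss, and 0.30 to 0.35 SD only in the extreme case. Neither direction nor size can be fixed from the protocol, and power is adequate at the planned loss. It still merits correction because it touches the primary comparison and uncollected scores cannot be restored.

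**What to change.** 1. Reconcile {10}, {11b}, {14}, {20a} and {20c}.
2. State that meeting a drop-out criterion bears only on the allocated treatment, or is flagged in the data, and does not end follow-up. This alters no clinical rule; what happens to treatment remains for the investigators to settle.
3. State that the pain NRS is still collected at every planned assessment from all randomised patients, unless they withdraw consent for data collection.
4. Replace *Not applicable* in {20c} with a primary method that keeps all randomised patients. One choice is a likelihood-based repeated-measures model with baseline NRS, gender, group, visit and group-by-visit. As that model alone omits patients with no post-baseline score, add multiple imputation for them. Multiple imputation throughout would also serve.
5. Add one delta-adjusted sensitivity analysis that worsens the imputed scores of those lost, with the shift allowed to differ by arm.

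The cost is rewording, a few extra follow-up questionnaires and slightly more analysis. The sample size need not change for this point.

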### Relevant concomitant care permitted or prohibited during the trial {11d}

Relevant concomitant care and interventions are prohibited during the trial.

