### Primary outcome

The pain will be assessed through a self-reported questionnaire. This questionnaire will be used for pain assessment at baseline, post-treatment, and at 1 and 4 months follow-up:
A Numerical Rating Scale (NRS) for pain ranging from 0 “no pain at all” to 10 “worst imaginable pain” (“How would you rate your low back pain, on average, over the last 3 days?”) [37].

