### Plans to promote participant retention and complete follow-up {18b}

Not applicable

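### Other treatment and eligibility violations count as drop-out after randomisation, with no statement that outcomes are still collected; this conflicts with the promised analysis of all randomised patients

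*Protocol article*

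**What the plan says.** Eligibility criteria {10} gives entry criteria, exclusion criteria and then a separate list of drop-out criteria. That list includes "participate in any other treatment during the interventions, inclusion or exclusion criteria are violated". Its other two items are a condition that interferes with treatment or assessment, and the patient's own request to leave the trial.

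On timing, Trial design {8} states: "The outcome will be assessed at baseline, after 6 weeks of treatment, and at 1 and 4 months follow-up". The Primary outcome section says the same of the pain NRS: "This questionnaire will be used for pain assessment at baseline, post-treatment, and at 1 and 4 months follow-up".

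On analysis, section {20a} says that the primary and secondary outcomes "will be based on the intention-to-treat principle including all randomized patients", and adds: "A model including baseline as continuous covariate and group as fixed factors will be used".

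On concomitant care, section {11d} says: "Relevant concomitant care and interventions are prohibited during the trial". The sections on discontinuing allocated treatment {11b}, on retention and complete follow-up {18b}, and on non-adherence and missing data {20c} are each answered as not applicable.

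**The concern.** A rule that takes randomised patients out because of what they do after randomisation works against an intention-to-treat comparison, unless those patients are still measured. No section says that they are.

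The other-treatment criterion matters most. Patients whose back pain is not improving are the likeliest to look for other care, so removal on that ground may be related to the primary outcome. It may also differ between arms: the experimental arm includes training in coping and in managing pain flare-ups, which could change care-seeking. The NRS comparison would then be between selected subsets of the two arms. An analysis plan written later can choose how to handle missing scores, but it cannot recover scores that were never collected.

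**Working it through.** **Reading the sections together**

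1. Sections {6b} and {16a} place consent, baseline measurement and randomisation before treatment. Other treatment during the interventions is therefore a post-randomisation event. The eligibility criterion carries no timing, but it sits in the drop-out list and not in the exclusion list.
2. Treatment lasts six weeks. The NRS is taken at baseline, post-treatment, 1 month and 4 months. A patient dropped during treatment and not assessed later has a baseline score only.
3. A model with follow-up NRS as response, baseline as covariate and group as factor needs a follow-up value. It cannot include that patient, whichever follow-up time is analysed.
4. Drop-out could mean stopping therapy only. Three features of the text count against this. The list includes the patient's request to leave the trial. Its first item covers conditions that interfere with assessment as well as with treatment. Stopping therapy has its own section {11b}, which is marked not applicable.
5. The explicit other-treatment clause covers the six weeks. Section {11d}, and the exclusion criterion in {10} on other therapies during the research, could extend it into follow-up. A patient dropped then would lose the later scores but keep the post-treatment one.

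**Size, as an illustration**

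No figure in the plan is disputed. The inputs from the Sample size section {14} are 35 patients per arm and a 10% allowance for loss to follow-up (0.10 × 70 = 7 patients). The section does not attribute that allowance to the drop-out criteria. The rest is assumed: kc control and ke experimental patients are removed, and they are on average d SD worse on NRS than their whole arm, with d from 0.5 to 1.

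Removing k of 35 patients who are d worse lowers the mean of those who remain by d × k/(35 − k). The bias in the between-arm difference is therefore

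bias = d × [kc/(35 − kc) − ke/(35 − ke)],

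and the unadjusted standard error, in SD units, is

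SE = √[1/(35 − kc) + 1/(35 − ke)].

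| Removed, kc:ke | Bracket | Bias, d = 0.5 | Bias, d = 1 | SE | Bias/SE |
|---|---|---|---|---|---|
| 2:2 | 2/33 − 2/33 = 0 | 0 | 0 | 0.246 | 0 |
| 2:0 | 2/33 − 0 = 0.0606 | 0.030 | 0.061 | 0.243 | 0.12–0.25 |
| 3:1 | 3/32 − 1/34 = 0.0643 | 0.032 | 0.064 | 0.246 | 0.13–0.26 |
| 4:3 | 4/31 − 3/32 = 0.0353 | 0.018 | 0.035 | 0.252 | 0.07–0.14 |
| 5:2 | 5/30 − 2/33 = 0.1061 | 0.053 | 0.106 | 0.252 | 0.21–0.42 |

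A positive value means that more control patients with poor outcomes were removed, so the benefit of the experimental therapy is understated. With the arms exchanged the sign reverses and the benefit is overstated.

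**The case against.** The strongest reply is that the conflict is conditional. The article never says that dropped patients leave the analysis, and it schedules assessments without excepting them. If drop-out ends therapy only, nothing conflicts. The full protocol, the flow chart and the assessment schedule are not shown, and an article may leave continued follow-up to them. The not-applicable entries look like filler, since data management and confidentiality carry them too. The bias mechanism fits other treatment better than eligibility violations, which should be few after screening and which, if present at entry, cannot be caused by the assigned arm. Finally, the illustration uses assumed counts and an assumed deficit, gives small biases, and in its 5:2 case assigns the whole 10% loss to these criteria.

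Much of this stands. The conflict is conditional, the not-applicable entries do not show a decision to stop follow-up, the mechanism is weaker for eligibility violations, and the size is modest and unknown in direction.

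It does not remove the point. The article states the drop-out rule outright, so the complaint is about what is written and not about missing detail. The list reads as leaving the trial, for the reasons given above. The two criteria also overlap: having other therapies is itself an exclusion criterion, so breaching it triggers the eligibility clause as well. Whether removed patients are still measured is a matter of trial conduct that must be settled before the visits are missed.

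**Conclusion.** The concern holds. The drop-out rule and the promise to analyse all randomised patients fit together only if dropped patients continue to be assessed. Nothing says so, and the wording of the list points the other way. This should be corrected.

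The conclusion rests on drop-out ending assessment, which the text suggests but does not state. The size cannot be determined from the documents. Under the assumed counts and a deficit of 0.5 to 1 SD, the bias lies between 0 and about 0.11 SD, or up to about 0.4 of a standard error, and its direction depends on which arm loses more patients. That alone would not overturn a clear result, but it could move a borderline one, and it would mean that the reported comparison is not the one promised.

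**What to change.** In Eligibility criteria {10}, replace the two drop-out items with wording such as:

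> *Other treatment, or an eligibility violation found after randomisation, is recorded as a protocol deviation and may stop trial therapy. The patient is still assessed post-treatment and at 1 and 4 months and is analysed in the randomised group. Only withdrawal of consent ends data collection.*

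Align section {11b} with this by stating when trial therapy may be stopped, and section {20c} by stating that non-adherent patients are analysed as randomised.

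The cost is a wording change in three sections, with the ethics approval that section {25} requires for modifications. It adds no visits or measures beyond those already scheduled. The downside is that patients who used other treatment stay in the comparison, which may dilute the contrast between the therapies. That dilution is part of the intention-to-treat comparison the protocol has already chosen.
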